**Methods:**

Prospective multicenter study. Patients aged between 18-75 years visited at Primary Care consultations will be included according to a randomization schedule to reach the sample size (198). The study involves 4 Sleep Lab Units and 6 Primary Care Centers in Barcelona. Two models of evaluation will be used: one in the Primary Care center and the other in the Sleep Lab Units. **Outcomes:** anthropometric data, cardiovascular history and risk factors, self-assessed questionnaire of sleep disorders, ambulatory monitoring study data and polygraphic/polysomnographic data. **Statistical analysis:** Calculation of the area under the curve (AUC) of the ROC curve (Receiver Operating Characteristics). The best clinical prediction model will be detected by using logistic regression. Variables with clinical significance in the bivariate analysis and variables considered clinically relevant will be included. The resulting model will be validated with the goodness-of-fit test (Hosmer and Lemeshow test). **Cost analysis:** Methodology according to Pietzoch JB et al. Sleep 2011; 34: 695-709.

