## **General and specific objectives**

### General objective:

The main purpose of this project is to develop and validate a work-model for Primary Care for identifying patients with OSA, based on clinical variables and an ambulatory monitoring study.

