### Sample size

The sample size has been calculated considering a minimum prevalence of 25% of OSA in the population attending Primary Care Medicine. Assuming 15% of losses to follow-up, an error of 5% and a power of 90%, a total sample of 198 patients was estimated as necessary to achieve a sensitivity of 90%.

According to the methodology proposed by Chai-Coetzer et al. (Thorax 2011; 66: 213-219), the screening study will be carried out taking into account clinical probability based on the Berlin Questionnaire (Netzer NC. Chest 2003; 124:1406-14). The study will be carried out in all patients with a high probability of OSA but in only 1 of 3 patients with a low probability. Therefore, a minimum of 396 valid questionnaires must be completed.

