#### Data management and analysis

The main objective of this study is to obtain a sufficiently accurate calculation of the area under the curve (AUC) of the Receiver Operating Characteristics (ROC) curve. The expected sensitivity value is high, close to 90%. With this number of cases the accuracy of the AUC will not be less than 10%. In all cases, the interval confidence of calculated rates is assumed to be 95%.

A descriptive analysis will be performed using means, medians, confidence intervals, interquartile ranges for quantitative variables and table of frequencies for qualitative variables. In qualitative variables, the Chi-square test or Fisher exact test will be used for bivariate analysis. In the case of quantitative variables, the T-test or Mann-Whitney U test will be performed according to normal distribution.

Finally, logistic regression will be used to find the best clinical prediction model. Variables showing clinical significance in the bivariate analysis and those considered clinically relevant will be included. A goodness-of-fit test (Hosmer Lemeshow test) will be performed to validate the resulting model. The AUC of the ROC will be used to calibrate the model.

In all cases, the significance level will be, as usual, 5% ( $\alpha = 0.05$ ), bilateral approach.

We will use IBM-SPSS (V. 21.0) software to perform the analysis.

In the analysis of costs we will consider the direct costs of all the tests (ambulatory monitoring study, polygraphy or polysomnography), staffing costs, the amortization of the devices, the transfer of the patients and the number of visits. We will also take into account the false-positive and negative diagnosis (*Pietzoch JB et al. An integrated Health-Economic Analysis of Diagnostic and Therapeutic strategies in the treatment of moderate to severe obstructive sleep apnea. Sleep 2011;34: 695-709*).

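### Hosmer-Lemeshow cannot validate the logistic model and the AUC cannot calibrate it, so the plan as written does not deliver the validation named in its general objective

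*Protocol*

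**What the plan says.** The general objective is to "develop and validate a work-model for Primary Care for identifying patients with OSA" (Protocol, General objective).

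Under Data management and analysis, the model is a logistic regression. Its variables are those that stand out in bivariate analysis plus those judged clinically relevant, with no limit on their number. A Hosmer-Lemeshow test "will be performed to validate the resulting model. The AUC of the ROC will be used to calibrate the model". The Methods paragraph of the summary repeats the first half: "The resulting model will be validated with the goodness-of-fit test (Hosmer and Lemeshow test").

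One sample is described: "Assuming 15% of losses to follow-up, an error of 5% and a power of 90%, a total sample of 198 patients was estimated" (Sample size). Its stated target is 90% sensitivity. The protocol mentions no split, resampling, shrinkage or second sample. What the section Design and Validation Time calls validation is the comparison of the Primary Care and Sleep Unit assessments in the same people. It is not a test of the fitted model in other people.

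**The concern.** Validating a prediction model means estimating how it performs in patients who did not shape it. Hosmer-Lemeshow, run on the fitting data, compares observed and fitted counts by risk group. The fitting step has already pulled those counts together, so p>0.05 says nothing about new patients.

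Calibration means agreement between predicted and observed risk. The AUC depends only on the ranking of predictions and cannot show such agreement.

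At stake is the main claim of the study. The Rationale expects Primary Care physicians to use the model to rule out OSA. A model whose AUC and sensitivity are overstated, and whose risks are too extreme, could pass both stated checks.

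**Working it through.** **1. Cases available.** Inputs from Sample size: prevalence 25%, loss 15%, error 5%, power 90%, target sensitivity 90%. The test is two-sided ("bilateral approach", Data management and analysis). No null sensitivity is given; assume 70%.

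- Cases = ((1.960·√(0.7·0.3) + 1.282·√(0.9·0.1)) / 0.20)² = (1.283/0.20)² = 41.1, so 42.
- 42/0.25 = 168 evaluable; 168/0.85 = 197.6, so **198**, as stated.

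The match does not identify the method. A precision formula with half-width 9 points gives 1.96²·0.09/0.09² = 42.7, so 43 cases; 43/0.25 = 172; 172·1.15 = 197.8, also 198.

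**2. AUC precision.** The protocol says "With this number of cases the accuracy of the AUC will not be less than 10" per cent. With 42 cases and 126 non-cases, the Hanley-McNeil 95% half-width is 0.097 at AUC 0.70 and 0.065 at AUC 0.90. Read as a half-width of at most 10 points, the statement holds. It covers sampling error only, not optimism.

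**3. Cases per candidate.** Outcome Measures lists about 25 candidates: 6 anthropometric and socio-demographic, 9 history and risk factors, drug treatment, symptom questionnaire, Berlin, Epworth, spirometry and 5 ambulatory-study variables. 42/25 = 1.7 cases per candidate.

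This is a floor. The prevalence is described as a minimum, and all Berlin-high but only 1 in 3 Berlin-low patients are studied. From h + l = 396 and h + l/3 = 198, l = 297 and h = 99, so 99 of each are studied. If every case were Berlin-high, cases would be 396·0.25·0.85 = 84, or 84/25 = 3.4 per candidate.

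**4. AUC and calibration.** In one simulated data set, the AUC was 0.796 for a score s, for 3s − 2 and for a logistic transform of s. Calibration differs across the three; the AUC does not.

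**5. Hosmer-Lemeshow and optimism.** Simulations with 168 evaluable patients and 200 to 400 runs per setting. All effect sizes and correlations are assumptions. The last column is the share of runs with p>0.05 in the fitting data.

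| Setting | AUC, same patients | AUC, new patients | Calibration slope, new | p>0.05, same data |
|---|---|---|---|---|
| 25 independent candidates, 4 real, kept if p<0.05 | 0.79 | 0.71 | 0.67 | 94% |
| 27 independent, p<0.05 plus 6 forced, three scenarios | 0.82; 0.86; 0.78 | 0.72; 0.79; 0.66 | 0.5 to 0.67 | 91 to 96% |
| 10 independent, 4 real, kept if p<0.05 | 0.77 | 0.73 | 0.79 | 95% |
| 25 independent, 4 real, all entered | 0.86 | 0.69 | 0.36 | 94% |
| 25 pure noise, all entered | 0.76 | 0.50 | 0 | 95% |
| 25 candidates, dominant ambulatory AHI (log-odds 1.5 per SD), 6 forced | 0.88 | 0.81 | 0.64 | 94% |
| Same, log-odds 2.5 | 0.93 | 0.88 | 0.68 | 94% |
| Same, log-odds 2.5, prevalence 50% | 0.92 | 0.88 | 0.73 | 93% |
| 25 correlated, dominant ambulatory AHI, p<0.05, prevalence 25% | 0.91; 0.96 | 0.86; 0.93 | 0.69 to 0.78 | not recorded |
| Same, prevalence 40% | 0.91; 0.96 | 0.87; 0.94 | 0.69 to 0.78 | not recorded |

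Prevalence is 25% unless stated. With five prespecified variables the AUC optimism fell to 0.02 to 0.025.

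For the first row, the same models tested on 168 new patients gave p>0.05 in only 48% of runs. The test stays silent because it is applied to the fitting data.

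**6. Sensitivity, if the cut-off is the Youden point in the same data** (an assumption). Same patients against new patients, for the three dominant-AHI rows with forced variables: 0.83 vs 0.68, 0.89 vs 0.76 and 0.86 vs 0.79.

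**7. Does the remedy work?** In 60 runs of 100 bootstraps that repeated the selection, the corrected AUC was 0.724 against a true 0.719; the apparent AUC was 0.812.

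**The case against.** - **The optimism may be small.** The ambulatory AHI measures nearly the same quantity as the reference AHI, sensitivity near 90% is expected, and the candidates are correlated. Enrichment also yields more than 42 cases. This stands: 0.07 to 0.12 is the pessimistic end. Yet slopes stay at 0.64 to 0.78 with bivariate selection from the full candidate list, and Hosmer-Lemeshow still passes wherever it was recorded.
- **Not every AUC is affected.** A reader might infer that the study's headline AUC is inflated. The protocol does not say that the AUC of its main objective is the model's. The first specific objective concerns the device itself, and an unfitted device AHI has no selection or fitting optimism.
- **Some steps are inferred.** No cut-off rule is stated, so the sensitivity figures are conditional. Evaluation in the same patients follows from the single sample but is not said in words.
- **Resampling details belong to a statistical analysis plan.** Agreed: their absence alone is no finding. Here the protocol names the validation and calibration methods and assigns them wrongly, so a later plan could correct them only by contradicting it.
- **The text reads as a translation, and calibrate may loosely mean assess.** This softens the AUC half. It does not help the Hosmer-Lemeshow half, which appears twice.

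**Conclusion.** The two roles are wrong as written, and that needs no simulation. For the fitted model, the plan cannot meet the validation part of its general objective.

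The size of the consequence depends on assumptions about predictor strength and the number of variables entered. AUC optimism is about 0.02 to 0.05 with a very strong ambulatory AHI and about 0.07 to 0.12 with many weaker predictors. At its larger end it is similar to the 0.065 to 0.097 half-width from sampling error. In either case Hosmer-Lemeshow gives p>0.05 in over 90% of runs.

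A reader might go further and infer that validation will be declared almost regardless of how the model performs. The document does not support that certainty: it fixes neither the number of variables nor their strength, and a small model led by the ambulatory AHI would lose little in new patients. What holds is that the stated checks would not tell such a model from an overfitted one.

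**What to change.** In Data management and analysis, and to match in the summary's Methods paragraph, replace the statements on validation and calibration with text to this effect:

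*The Hosmer-Lemeshow test is a descriptive check of apparent fit. The AUC describes discrimination. Internal validation uses a bootstrap that repeats every modelling step, including variable selection and any data-driven choice of cut-off. Optimism-corrected AUC, sensitivity and specificity are the reported model results, with calibration intercept, slope and plot. The model will be described as internally validated only.*

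State separately that the AUC of the unfitted ambulatory AHI needs no such correction.

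A leave-one-centre-out check is not worth adding: 168/6 = 28 patients and 42/6 = 7 cases per Primary Care centre are too few for an informative AUC.

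Cost: a change of wording and a few hours of programming, possibly outside SPSS 21, with no new patients or visits. The downside is a less favourable reported AUC.

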#### **Quality Control**

Each investigator will ensure the accuracy and the integrity of the data and the reports. The data collected in the Data Collection Notebook, derived from source-documents, will be

concordant, and discrepancies should be justified. The research coordinator of the study will store the documents for at least 5 years after the completion. At the request of a monitor, auditor, Ethics Committee or Health Authority, the research coordinator will have available all the files related to the study. The coordinator will allow direct access to all the data and documents to perform monitoring, audit, a review by the Ethics Committee and test inspections by the competent authorities.

## Limitations

- Limitations of RP: sleep time is not equivalent to study time and this can underestimate the values. To avoid this, we will take into account the quality of sleep provided by the patient. Thus, this aspect will not significantly limit the main objective: to differentiate patients with severe disease or mild disorders.
- Acceptance rate of participation: In a previous study with similar characteristics, the acceptance rate of participation was 40% of the survey respondents. Considering the large population usually attended at Primary Care centers in the urban area of Barcelona, this is not an expected limitation for reaching sample size. We must take into account that patients accepting their inclusion in the study could be those with greater comorbidity. This could give rise to a bias in the sample.

## Time Planning

| TASKS                         | Planning |  |  |  |      |  |  |  |      |  |  |  |      |  |  |  |
|-------------------------------|----------|--|--|--|------|--|--|--|------|--|--|--|------|--|--|--|
|                               | 2015     |  |  |  | 2016 |  |  |  | 2017 |  |  |  | 2018 |  |  |  |
| Project coordination meetings |          |  |  |  |      |  |  |  |      |  |  |  |      |  |  |  |
| Primary Care staff training   |          |  |  |  |      |  |  |  |      |  |  |  |      |  |  |  |
| Recruitment Period            |          |  |  |  |      |  |  |  |      |  |  |  |      |  |  |  |
| End of study at Sleep Unit    |          |  |  |  |      |  |  |  |      |  |  |  |      |  |  |  |
| Results analysis              |          |  |  |  |      |  |  |  |      |  |  |  |      |  |  |  |
| Results publication           |          |  |  |  |      |  |  |  |      |  |  |  |      |  |  |  |

## **Considerations concerning patient information and consent form**

The study will be conducted in strict accordance with international ethical guidelines for medical research in humans. Each investigator is responsible for ensuring that the study is conducted according to the standards set out in the Declaration of Helsinki.

Before starting the study, the Ethics Committee of each participating center must approve the study protocol, the information letter and the consent form.

## **Resources**

The Sleep Unit at Hospital de la Santa Creu i Sant Pau, the coordinator of this study, has two Pulmonologists and two specialized nurses who are responsible for all respiratory diseases related to sleep. It also has two additional nurses who perform overnight sleep studies and CPAP titration. In this Unit, we perform about 1500 sleep studies per year, including outpatient studies, and attend 3,000 consultations related to OSA. There are four hospitalization beds, two PSG devices, 4 RPs, 2 single-channel devices and 3 CPAP titration devices.

The other two Sleep Units located in Hospital Vall d'Hebron (Multidisciplinary Sleep Unit) and Hospital del Mar, also have the necessary facilities and experience in the use of the techniques involved in this project. All of these procedures are part of their routine clinical practice.

All three hospitals have a great commitment to the transfer of part of this assessment to outpatient care medicine.

The Primary Care teams involved have the support of a variable number of physicians and nurses who are responsible for the first level of medical attendance. At the Primary Care level there are computerized medical records registering health problems, medical examinations (i.e. spirometric data), chronic-disease monitoring devices and diagnostic assistance. All the Primary Care centers have spirometers and trained nurses. The Research Group of Respiratory Diseases in Primary Care (IDIAP) also has professionals that provide methodological support to this project. Both Research Institutes (Sant Pau and IDIAP Jordi Gol i Gurina) also provide the support needed to carry out this study.

## **Experience of the Research Team**

This project is coordinated by the Sleep Unit of Hospital de la Santa Creu i Sant Pau. In recent years, the research activity of this Unit has been focused on the study of clinical aspects related to sleep respiratory disturbances (SRD). The three Sleep Units involved in this project work under the *Spanish Sleep and Breathing Group* and are participating in several multicenter studies evaluating new methods of study the SRD and their clinical consequences. These studies have been published in high impact journals and have had a direct effect on the development of clinical practice guidelines.

The Sleep Unit of Hospital de Sant Pau is part of the *CIBER of Respiratory Diseases*.

One aspect that gives value and feasibility to this project is the inclusion of distinguished Primary Care professionals. Most of the Primary Care professionals involved are part of the Research Group of Respiratory Diseases in Primary Care (IDIAP). The group is composed of professionals from different Primary Care centers in the area called “Dreta de l'Eixample” in Barcelona. Their main objective is to standardize and coordinate the assessment of this disease at every health-level in order to achieve a proper use of all the available resources.

## **Practical applicability of the results**

Nowadays, Primary Care needs to play a more important role in respiratory sleep disorders, not only by improving the level of clinical suspicion, but also by monitoring patients previously diagnosed and under treatment.

The incorporation of a clinical screening model and the validation of ambulatory monitoring studies at the Primary Care level would mean an improvement in the management of patients with OSA. This could provide greater flexibility in the diagnostic process and a decrease in waiting times. This screening model tries to save hospital visits and unnecessary tests, thereby avoiding the waste of resources. This would reduce the costs related to the disease.
